## Discussion

The present study has been designed to assess the effects of training GPs in early identification and a proactive palliative care approach regarding patients with COPD, CHF or cancer.

### Strengths

Up to now, hardly any data are available about implementing the 2002 WHO-definition for palliative care. To our knowledge this is the first intention to treat RCT that assesses the effect of training GPs in early identification and using a proactive holistic palliative care approach, which are the main aspects of this definition. The training for the GPs in the intervention group was standardised and piloted, to minimize differences between the two trainers and to be available for future courses. The tools that the GPs in the intervention group could use for helping to identify palliative patients in an earlier stage than usual and to structure the proactive care planning, were developed in a scientifically sound way. Results will be published in peer-reviewed scientific journals and will be communicated to relevant clinician associations.

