### Participants

GPs in two comprehensive cancer centre (IKO and IKZ) regions in the South-East of the Netherlands were invited by mail to participate in the study. After one month a reminder was send to non-responders. Excluded were GPs who are consultant in palliative care or who are locum. GPs that wanted to participate were stratified for degree of urbanization and working hours (part-time or full-time) and were randomized assigned to the intervention or the control condition by an independent statistician. To prevent contamination, those GPs working together in the same practice were placed in the same study group.

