### Data collection

At the start of the study (t = 1), GPs in the intervention group were asked to use RADPAC to screen the medical records of all patients in their practice to identify patients with COPD, CHF or cancer who potentially could benefit from a palliative care approach. They were instructed to continue to use RADPAC each time new data of a patient with CHF, COPD or progressive cancer was available. In 2011, anonymous data were collected retrospectively from the medical records of all patients that had a non-acute death during the intervention period, as well in the intervention as in the control practices (t = 2). All deceased patients who were diagnosed with CHF, COPD and/or cancer were included (Figure 2). Each non-planned (out of hour) contact and hospital or nursing home admission during the study was derived from the medical record and registered as well as place of death and if the patient had been identified as being in the palliative trajectory. Besides, qualitative data were collected concerning proactive care planning in both study groups.

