### Outcomes

GPs of both study groups were invited to extract data of all patients that died during the observational period from the medical records: demographics, disease history, place of death, hospital admissions and out of hours consultations. Of each participating GP, demographic characteristics, practice characteristics and their interest in palliative care were collected (Table 3).

**Table 3 T3:** Baseline characteristics participating GPs^# ^(n = 133)

*Characteristics of general practitioners *	
Age - yr	48,2 ± 8,1

Gender male sex - no.(%)	81 (60, 9)

Working week fulltime - no. (%)	70 (52, 6)

Experience - no. (%)	

≤ 1 year	2 (1, 5)

2 - 5 years	14 (10, 5)

6 - 10 years	21 (15, 8)

≥ 10 years	94 (70, 7)

Missing	2 (1, 5)

Interest in palliative care*	8, 14 ± 1, 12

Missing	3

Estimation of own capability**	6, 83 ± 0, 92

Missing	3

*Characteristics of practice *	

Practice form - no. (%)	

Single-handed	28 (21, 1)

Dual	53 (39, 8)

Group and health centres	52 (39, 1)

Missing	0

Degree of urbanisation - no. (%)	

Very	46 (34, 6)

Moderate	28 (21, 1)

Less	41 (30, 8)

No	18 (13, 5)

Missing	0

Size of practice Fte-average practice^+^	1728 ± 409

Missing	1

*Palliative care*	

Palliative patients/y - no. (%)	

≤ 2 patients	10 (7, 5)

3 - 5 patients	72 (54, 1)

5 - 9 patients	43 (32, 3)

≥ 10 patients	6 (4, 5)

Missing	2 (1, 5)

Use of consultant palliative care - no. (%)	

Yes	105 (78, 9)

No	25 (18, 8)

Missing	3 (2, 3)

^#^Plus-minus values are means ± SD

^+ ^Size of practice = fulltime-equivalent/average practice (= 2350 patients)

*Interest in palliative care, visual analogue scale, rang 0, indicating no interest, to 10 very much interest.

** Estimation of own capability, visual analogue scale, rang 0, indicating not capable, to 10 very much capable.

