### Data management and plan of statistical analysis

All data were entered in a database and analysed with SPSS 16.0. In both study groups, all patients who died during the inclusion and observation period of the study of a non-acute death, were included in the retrospective analysis. Intervention and control group will be compared on the main outcomes (place of death, number of transitions and out of hours contact, amount of identified patients). Recruitment rates and drop-out rates will be calculated. In case denominators prove to be significantly correlated with the outcome of the main study question, an Anova will be performed to identify potential related or independent factors. Multilevel analysis will be performed.

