### Weaknesses

Those GPs that were interested to take part in the study, probably have a special interest in palliative care. Besides, as there is a lot of attention for proactive palliative care in medical journals and in Dutch policy, GPs in the control group might be influenced by new information or followed courses. This implies that it might be difficult to find significant differences between intervention and control group. As patients were identified by their own GP, we were not able to influence this process directly.

We did not choose to collect prospective patient data in the control group, as this would be a sort of intervention. Therefore, effect measurement took place retrospectively. GPs in both intervention and control group were asked to collect retrospective data from their digital patient information system. This implies that we do not have patient data of non-responding GPs.

We performed a multifaceted intervention: a combination of training GPs and offering them tools to facilitate early identification and proactive care planning. Usually, multifaceted interventions are more effective than single interventions,[36] but the relative impact of each component of the intervention cannot be established.

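### The trial is labelled intention to treat, but its analysis set is the patients of responding GPs, analysed as randomised

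*Protocol article*

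**What the plan says.** The Strengths section of the protocol article makes the claim: "To our knowledge this is the first intention to treat RCT that assesses the effect of training GPs in early identification". The section on data management and statistical analysis describes a complete set of deaths: "all patients who died during the inclusion and observation period of the study of a non-acute death, were included in the retrospective analysis". The Data collection section limits this by diagnosis but not by GP response: "All deceased patients who were diagnosed with CHF, COPD and/or cancer were included".

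Two other places describe how the data arrive. Under Outcomes: "GPs of both study groups were invited to extract data of all patients that died during the observational period from the medical records". Under Weaknesses: "GPs in both intervention and control group were asked to collect retrospective data from their digital patient information system", followed by "This implies that we do not have patient data of non-responding GPs".

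The Participants section says that GPs were the units assigned, and that "those GPs working together in the same practice were placed in the same study group". The analysis section also says that recruitment and drop-out rates will be calculated. No response rate, overall or by arm, appears in the article.

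**The concern.** An intention-to-treat comparison rests on outcomes from everything that was randomised, or on a stated way of dealing with what is missing. Here the randomised GP also supplies the outcome data. A GP who does not answer the invitation removes part or all of a randomised unit, with every eligible death in it, after allocation.

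The design gives reasons why response could be selective by arm. Intervention GPs had a five-hour training, a coaching session for each included patient and two peer group sessions; control GPs gave usual care and were offered training after the study closed. Given such an intervention, GPs know which arm they are in, and each extracts the results by which the training is judged. If the decision to return data is related to those results differently in the two arms, the comparison is biased.

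The Weaknesses section reports the missing data but does not mention this consequence. The effect on results that it does discuss is that a difference may be hard to find; selective response could also produce a difference where there is none. The article says that its methodology will be the reference for later publications, so the label is likely to be carried forward.

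**Working it through.** **1. The statements side by side.**

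| Section | Statement | What it requires |
|---|---|---|
| Strengths | Intention-to-treat RCT | Outcomes for all randomised GPs, or a stated method for the missing ones |
| Data management and analysis | All non-acute deaths in both groups included | Every randomised GP returned data |
| Outcomes | GPs invited to extract the records | Return depends on the GP |
| Weaknesses | No patient data from non-responding GPs | Deaths under those GPs are absent |

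The first two rows agree with the last two only if every randomised GP responded. The article does not say that they did.

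**2. The plan's own figures.** No stated figure tests this point. The sample size of 96 patients rests on a 20% reduction in out-of-hours contacts, without a baseline or standard deviation, so it cannot be uniquely reproduced. The 20%, read as relative, serves below only as a yardstick.

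**3. What selective response could do.** All inputs in this step are assumed, and there is no true effect.

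*Illustration A: response depends on GP type in one arm only.* Two equally common types of GP have home-death shares of 60% and 40% and mean contacts of 3 and 5. Response is 90% and 50% in the intervention arm, and 70% for both types in the control arm.

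- Home death, intervention: (0.9×0.6 + 0.5×0.4)/1.4 = 0.74/1.4 = 52.9%. Control: (0.7×0.6 + 0.7×0.4)/1.4 = 0.70/1.4 = 50.0%. Spurious gain: 2.9 points.
- Contacts, intervention: (0.9×3 + 0.5×5)/1.4 = 5.2/1.4 = 3.71. Control: (0.7×3 + 0.7×5)/1.4 = 5.6/1.4 = 4.00. Spurious change: 3.71/4.00 − 1 = −7.1%.

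Overall response is 70% in both arms, so equal drop-out rates would not reveal this bias. Conversely, 90% response from both types in one arm and 60% from both in the other gives no bias: (0.9×0.6 + 0.9×0.4)/1.8 = (0.6×0.6 + 0.6×0.4)/1.2 = 50%. The harm comes from selection that differs by arm, not from unequal rates alone.

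*Illustration B: a range.* Let a share *r* of patients be lost in the intervention arm only, and let the lost patients have *k* times the contacts of those retained. With the full-arm mean set to 1, the retained mean is 1/((1 − *r*) + *r·k*). The apparent change in contacts is that value minus 1.

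| *r* | *k* = 0.5 | *k* = 0.8 | *k* = 1.25 | *k* = 1.5 | *k* = 2 |
|---|---|---|---|---|---|
| 10% | +5.3% | +2.0% | −2.4% | −4.8% | −9.1% |
| 20% | +11.1% | +4.2% | −4.8% | −9.1% | −16.7% |
| 30% | +17.6% | +6.4% | −7.0% | −13.0% | −23.1% |

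For example, *r* = 20% and *k* = 2 gives 1/(0.8 + 0.4) = 0.833, an apparent reduction of 16.7%. Losing the same patients in the control arm instead reverses the sign; losing them in both arms cancels the bias.

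**The case against.** The strongest reply is that the label has a proper meaning here. All non-acute deaths with an eligible diagnosis are to be analysed in the arm to which the GP was assigned, whether or not the patient was identified with the indicator card or discussed in a coaching session. That is analysis by allocation regardless of uptake, an important part of intention to treat, and this part of the reply stands. A reader might infer from the missing data that the trial is really a comparison by treatment received; nothing in the article supports that.

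Second, the gap is disclosed in the section directly after the claim. This also stands: the article hides nothing, and it would be wrong to say that the label assures readers that no bias can arise. But disclosure under Weaknesses does not make the unqualified statements under Strengths and in the analysis section correct.

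Third, unequal response between arms is not shown. Greater contact might make intervention GPs readier to respond; their heavier workload, or the training promised to control GPs, might work the other way. This stands too. Illustration A needs an assumed interaction between GP type and arm, and Illustration B assumes one-sided loss.

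Fourth, missing-data methods may be in a full protocol or analysis plan that is not shown. Their absence from an article is therefore no fault, and none is claimed.

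**Conclusion.** The point holds as a misstatement of the analysis set. Unless every randomised GP responded, the article describes patients of responding GPs, analysed as randomised, and should say so. With full response the label would be defensible.

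The size of any bias cannot be determined. Selective response by arm is a plausible risk of unknown direction. Under the assumptions shown, the apparent change in contacts when there is no effect runs from a 23% reduction to an 18% increase, against a design target of 20%. These figures show only that the issue is not negligible in principle. A reader might infer that response did differ by arm, or that the trial's result is biased; the documents support neither.

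**What to change.** - Under Strengths, replace *intention to treat* by *responding GPs analysed as randomised*, and limit the statement that all patients were included to the practices of responding GPs. Carry the same wording into the results report.
- Report the numbers of GPs and of practices randomised and responding, by arm. As Illustration A shows, these counts are necessary but not sufficient.
- Compare responders with non-responders within each arm on the Table 3 characteristics, such as interest in palliative care, self-rated capability, working hours and urbanisation. This assumes that the 133 participating GPs in Table 3 are those randomised, which should be confirmed. No item there is missing for more than three GPs.
- Unless the full plan already has one, add a sensitivity analysis adjusted for those characteristics or weighted by the inverse probability of GP response. It can correct only for selection on what was measured.
- A tipping-point analysis is optional: the number of deaths in non-responding practices is not held and would have to be assumed.

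The cost is a less favourable strength claim and modest extra analysis, mostly on data already collected.

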### Weaknesses

Those GPs that were interested to take part in the study, probably have a special interest in palliative care. Besides, as there is a lot of attention for proactive palliative care in medical journals and in Dutch policy, GPs in the control group might be influenced by new information or followed courses. This implies that it might be difficult to find significant differences between intervention and control group. As patients were identified by their own GP, we were not able to influence this process directly.

We did not choose to collect prospective patient data in the control group, as this would be a sort of intervention. Therefore, effect measurement took place retrospectively. GPs in both intervention and control group were asked to collect retrospective data from their digital patient information system. This implies that we do not have patient data of non-responding GPs.

We performed a multifaceted intervention: a combination of training GPs and offering them tools to facilitate early identification and proactive care planning. Usually, multifaceted interventions are more effective than single interventions,[36] but the relative impact of each component of the intervention cannot be established.

## Conclusion

The present study will increase the knowledge about the effect of training GPs in early identification and a proactive palliative care approach. This knowledge is of importance to improve palliative care for patients with COPD, CHF and cancer and their informal caregivers, as well as to empower the GP. Here, the study protocol is described and possible strengths and weaknesses and possible consequences have been outlined.
